## Abstract

**Background:**

Virtual Patients (VPs) are web-based representations of realistic clinical cases. They are proposed as being an optimal method for teaching clinical reasoning skills. International standards exist which define precisely what constitutes a VP. There are multiple design possibilities for VPs, however there is little formal evidence to support individual design features. The purpose of this trial is to explore the effect of two different potentially important design features on clinical reasoning skills and the student experience. These are the branching case pathways (present or absent) and structured clinical reasoning feedback (present or absent).

**Methods/Design:**

This is a multi-centre randomised 2x2 factorial design study evaluating two independent variables of VP design, branching (present or absent), and structured clinical reasoning feedback (present or absent).The study will be carried out in medical student volunteers in one year group from three university medical schools in the United Kingdom, Warwick, Keele and Birmingham. There are four core musculoskeletal topics. Each case can be designed in four different ways, equating to 16 VPs required for the research. Students will be randomised to four groups, completing the four VP topics in the same order, but with each group exposed to a different VP design sequentially. All students will be exposed to the four designs. Primary outcomes are performance for each case design in a standardized fifteen item clinical reasoning assessment, integrated into each VP, which is identical for each topic. Additionally a 15-item self-reported evaluation is completed for each VP, based on a widely used EViP tool. Student patterns of use of the VPs will be recorded.

In one centre, formative clinical and examination performance will be recorded, along with a self reported pre and post-intervention reasoning score, the DTI. Our power calculations indicate a sample size of 112 is required for both primary outcomes.

**Discussion:**

This trial will provide robust evidence to support the effectiveness of different designs of virtual patients, based on student performance and evaluation. The cases and all learning materials will be open access and available on a Creative Commons Attribution-Share-Alike license.

## Background

### Virtual patients

Virtual patients(VPs) can be defined as electronic representations of realistic clinical cases [1]. They have been proposed as being an ideal tool to teach clinical reasoning skills [2]. A recent literature review, and systematic review of the literature has highlighted a lack of evidence supporting individual design properties for virtual patients as in other elearning areas [3]. VPs are widely used in up to one third of US and Canadian medical schools, however until 2007 development costs were high [4]. Multiple tools now exist to author virtual patients Much of the focus until now was been on their utility as educational tools in comparison to traditional teaching, in keeping with other elearning research [5].

A range of software packages exist for case authoring including ‘CAMPUS’, University of Heidelberg [6]; ‘Labyrinth’ from the University of Edinburgh [7]; ‘Web-SP’ from the Karolinska Institute, Sweden [8]; and ‘vpSim’ from the University of Pittsburgh [9]. Other researchers used bespoke software solutions to author cases [10,11].

An international technology interoperability standard for VPs was adopted in 2009 by the Medbiquitous Consortium [12]. This benchmark allows the interoperability of VP cases between compatible software systems allowing authoring, editing and playing of cases [13]. This facilitates collaboration, research, open access and the upkeep of these electronic resources [14,15]. This has potentially changed the working definition of what a VP is, by re-defining properties and dimensions of VPs[16,17]. A European Commission funded study has produced self-reported evaluation scores to help evaluation, the EViP project [15].

There are numerous VP design properties identified in the literature [2] and their impact on the learning experience are poorly understood[3]. Of particular interest are, firstly, the use of branching case pathways [18], and secondly, the role of structured feedback to promote clinical reasoning. Branching cases are more difficult to construct, more expensive when compared with linear cases [4], and may have unpredictable effects on individual students [19]. Clinical reasoning teaching support provides structured approaches to clinical reasoning [20,21], which can be deployed in VPs. In the ‘SNAPPS’ approach [20], students summarise case findings, narrow a differential diagnosis, analyse the differential diagnosis by comparing and contrasting possibilities, and plan management.

A number of validated tools exist to evaluate clinical reasoning and student experiences with a VP. To measure clinical reasoning, tools include the Key Feature Problem [22,23], and the Diagnostic Thinking Inventory[24,25]. Other appropriate assessments include multiple-choice questions, Bayesian reasoning questions [25,26] and diagnostic proficiency [20].

In musculoskeletal medicine there is a challenge in meeting the needs of increasing student populations [27]. This is confounded by a lack of exposure to clinical cases [28] which can potentially be mitigated by the use of virtual patients.

### Problem statement and hypothesis

The influence of different design features in a VP is under-researched, although they can significantly affect the time and cost of VP production. A research study in this area would be able to answer this research question.

We hypothesise that the two important independent VP design variables, branching (present or absent), and structured clinical reasoning feedback (present or absent) are likely to influence students clinical reasoning in cases, and their user experience in terms of realism, engagement and learning value.

## Methods

### Objectives

The aim of this study is to evaluate how two independent VP design variables influence their effectiveness as an educational tool in musculoskeletal medicine. The specific objectives in the study are firstly to evaluate the performance of students exposed to different virtual patient designs in identical assessments of clinical reasoning skills. Secondly we aim to determine how different VP designs influence the student experience when using a VP. Finally we are attempting to explore the relationships between student performance in VP assessment metrics and other measurements of clinical skills, including written and clinical examinations.

### Study design

This is a randomised 2x2 factorial design study evaluating two independent variables of VP design, branching (present or absent), and structured clinical reasoning feedback (present or absent).

### Setting and participants

The setting is three university medical schools in the United Kingdom. These are the Warwick Medical School (WMS), the University of Birmingham Medical School (UBMS), and Keele Medical School (KMS). WMS runs a four year MBChB degree open only to graduate entry medical students, UBMS and KMS have a five year MBChB degree course, open to undergraduate entry medicine (UEM) graduate entry medical (GEM) students. The research project will run from 2011 to 2013.

### Virtual Patient software information technology

Virtual patient cases in the study are created to the Medbiquitous standard [12] using the XML programming language [29]. The software used to create and host the cases is DecisionSim® v2.0, developed by the University of Pittsburgh. The cases are compatible with open source VP systems such as Open Labyrinth [7]. Access to cases, participation, electronic consent, and post case evaluations will be controlled by the VP software, and content hosted on the University of Warwick virtual learning environment Internet pages. Students will be registered with and logged in to the software, allowing tracking of decisions and performance.

**Figure 1 F1:**
[figure not shown]
Flow diagram of study Proposed study protocol.

### Recruitment and baseline data collection

All eligible students will be invited to participate in the study. Inclusion criteria are students in the year group studying MSK medicine. The only exclusion criteria are students who do not volunteer or consent. Eligible students will be invited to attend an oral presentation and demonstration of the study, and given an approved study participant information sheet. Students who do not electronically record their informed consent will not be able to complete any cases, and are not considered to be participants. Students who consent will be considered to be study participants from this point onwards. At this point the baseline data collected from students will be gender, email address, student type (UEM/ GEM), year of study, and institution.

Additional data and information on other aspects of student performance will be collected from the examinations officer at WMS only. This includes student performance on formative clinical and written assessments at both at the end of the musculoskeletal block, and the end of year assessments.

### Intervention and Independent design variables

The intervention consists of students completing four VP cases sequentially. Each case takes approximately 30 minutes to complete. The cases focus on four core clinical musculoskeletal areas. These are large joint arthritis, back pain, polyarthritis, and connective tissue disease. The 2x2 factorial study design means that any cases can be designed in four different ways. The four case designs are: A) not branched+ no-feedback; B) branched+ no feedback; C) not branched+ feedback; D) branched+ feedback. Students will use all four of the case designs during the research (see Figure 1).

The first variable is branching pathways through the VP, present or absent. There are four branching points with three choices through the thirty-minute case. This gives a possible 81 core pathways (3^4) through the case in a branched form. The linear case has a single core pathway, with participants being redirected back to the core pathway irrespective of the decision made, for example by feedback from a supervising clinician in the case. The second variable is the use of structured feedback to promote clinical reasoning skills, present or absent. This will be in a predetermined approach through the cases at five key points through the case, based on the ‘SNAPPS’ approach [20], systematic approaches to help Bayesian reasoning [21], and symptom categorisation [31].

Cases will be piloted and tested by healthcare professionals and a cohort of students in one centre prior to the study commencing. For the study, students will complete cases at WMS and KMS is in the form of sequential teaching sessions to students, taking place in a computer cluster. Students at UBMS will complete cases during allocated self-study time during their musculoskeletal block.

Other than the described independent variables we will control for other design variables highlighted in a critical literature review [2].

### Inclusion and exclusion criteria

Inclusion criteria are students enrolled on the medical degree course and in the musculoskeletal teaching block in one of the medical schools in the study. Students must electronically sign consent to be included. Exclusion criteria are students from other year-groups. Students registered for a medical degree are required and assumed to have appropriate language and information technology skills.

### Blinding

Students will be blind to their group allocation. Investigator blinding for the purposes of the data analysis and allocation is not used. In the institution where clinical examination performance is recorded, none of the investigators examine within the clinical specialty (musculoskeletal medicine).

### Outcome measures

The primary outcome measures in this study are the performance in standardised composite clinical reasoning assessment using validated tools, and a modified self reported 15-item evaluation, reviewing four domains. These will be completed both during and immediately following each case. The secondary outcome measures are engagement and patterns of use within the cases and collected from the online environment (see Table 1). For each case, the composite clinical reasoning assessment consists of validated assessment of clinical reasoning. These 15 items are eight ‘key feature problem’ questions, one Bayesian reasoning question, two multiple choice questions on diagnosis, and four multiple choice clinical decision questions. For each case the content of these 15 items is identical, allowing comparison between case designs. This allows comparison of a case which is not branched with no structured feedback vs. the same case in a branched format with structured feedback.

**Table 1 T1:** Outcomes Measured during the study

***Institution***	***Outcomes for individual cases***	***Timing***
**All institions (WMS, KMS, UBMS)**		
**Primary Outcome Measures collected for each VP**		
*Validated clinical reasoning assessments.*	Key Feature Problems score (x/8)	Student completes during the case
	Clinical Decision (x/4)	
	Bayesian Statistical Question (x/1)	
	Working diagnosis (x/2)	
	(Total score x/15)	
*Self reported evaluation (EVIP)*	*EViP Questionnaire (multiple domains)*	After each case
	*Case Preference: reasoning (n from 4) learning (n from 4)*	On completion of all cases
	*Preference of case (learning)*	
	*Preference of case (realism)*	
**Secondary Outcome measures**		
*Other metrics collected in electronic environment*	Time spent per case (seconds)	During the case, recorded automatically
	Time spent per node (seconds)	
	Number of nodes visited	
	Case completion percentage.	
	Time spent per question (seconds)	
**WMS Only**		
*Validated self reported reasoning assessment (DTI)*	Baseline and Mean improvement	Immediately Pre-and post- intervention
*Summative assessment*	Written and clinical	1 week post intervention
*Formative assessment*	Written and clinical	End of the year

Student evaluation of each case will be collected using an electronic version of the EViP questionnaire, a fifteen item self reported evaluation. This explores exploring authenticity, professionalism, learning, and coaching through the case, using Likert scales with additional free text responses. Secondary outcome measures for each case are student’s patterns of use of the case, such as time taken per case, case completion rates, and time taken to complete individual decisions.

Additional data will be collected from one centre, WMS, to support the validity of the VPs as educational and assessment tools. This includes a pre- and post-test Diagnostic Thinking Inventory, a 41 item validated assessment of clinical reasoning ability [24]. Performance in summative and formative written and clinical assessments, measured one week following the VP case, and several months later will also be collected.

### Sample size determination

The authors agreed an important educational effect of a 5% difference in the score on validated assessments of clinical reasoning skills, and student self reported evaluations score. As no gold standard exists for the measurement of clinical reasoning skills, we have based the sample size calculation on performance for clinical reasoning on performance in the key feature problems (KFPs) integrated into each VP case. A previous study has shown mean KFP scores in a student population to be approximately normally distributed, with a standard deviation of 1.32 [32]. In this study where we will use 16 KFPs, a 5% difference in scores is considered significant, that is a difference in mean scores of 0.8, corresponding to a standardised effect size of approximately 0.6 (moderate to large). Based on these assumptions, we would require a total sample size of 88 students to detect this difference with 80% power at the (two-sided) 5% level. Assuming the effect size to be the same for both branching and feedback interventions, a sample size of 88 students would provide sufficient power to detect the main effects and an interaction effect that was twice as large as the assumed main intervention effect in the setting shown in Table 2.

**Table 2 T2:** Sample size calculation for Key Feature Problems outcomes, and student self evaluation scores

**Key Feature problems**					**Student self reported Evaluation scores**				
		Branching		*Total*			Branching		Total
		No	Yes				No	Yes	
Feedback	No	22	22	*44*	Feedback	No	28	28	*56*
	Yes	22	22	*44*		Yes	28	28	*56*
*Total*		*44*	*44*	***88***	*Total*		56	*56*	***112***

If the interaction between branching and feedback interventions is of same order of magnitude as the expected main effects then we would require a fourfold increase in the sample size to give a total of 352 students. [33]

For self-reported scores, where a previous study reported a standard deviation of 0.93, [34] a 10% difference in scores (with a maximum of 5) is considered significant, that is a difference in mean scores of 0.5, corresponding to a standardised effect size of approximately 0.5 (moderate). Based on these assumptions, we would require a total sample size of 112 students to detect this difference with 80% power at the (two-sided) 5% level (Table 2).

Therefore 112 students would be required to detect the main effects and large interaction effect of branching and feedback on self-reported scores. To detect an interaction effect of the same order of magnitude as the expected main effects would require a total of 448 students. The pool of students available for recruitment into this study is large at the three centres (WMS, n~160; UBMS, n~400; KMS, n~150). Given unforeseen recruitment problems and some loss to follow-up, a target of 112 students should be easily achievable to quantify the main intervention effects (branching and feedback) which are the primary focus of the study, with increasing recruitment above this target providing increasing power to detect potential interactions between the main effects.

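### The clinical-reasoning sample size rests on a 16-KFP score and independent groups, while the trial scores eight KFPs per VP in a 15-point composite and compares designs within students

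*Protocol article*

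**What the plan says.** The Sample size determination section of the protocol article sets the target effect: "The authors agreed an important educational effect of a 5% difference in the score on validated assessments of clinical reasoning skills". It gives the lack of a gold standard as the reason for planning on KFPs: "we have based the sample size calculation on performance for clinical reasoning on performance in the key feature problems (KFPs) integrated into each VP case". The spread is taken from a cited study: "A previous study has shown mean KFP scores in a student population to be approximately normally distributed, with a standard deviation of 1.32". Then comes the step at issue: "In this study where we will use 16 KFPs, a 5% difference in scores is considered significant", which the article turns into a difference of 0.8 points and a standardised effect of about 0.6. The result is that "we would require a total sample size of 88 students to detect this difference with 80% power at the (two-sided) 5% level". Table 2 sets this out as 22 students per cell and 44 v 44 for each main effect.

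Other sections describe a different score and a different layout:

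- **Score.** The Outcome measures section lists eight KFPs among the 15 items of each case. Table 1, under the primary outcomes collected for each VP, has "Key Feature Problems score (x/8" and "Total score x/15".
- **Analysed outcome.** The Outcome measures and Data analysis sections make the composite, not the KFP score, a primary outcome.
- **Exposure.** The section on the intervention and independent design variables has each student complete four VPs, one in each design.
- **Target.** The recruitment target of 112 comes from the self-reported evaluation score, not from the KFP calculation.

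**The concern.** The 16 carries the calculation. It converts the agreed 5% into 0.8 points, and 0.8 with the SD of 1.32 gives the effect of 0.6 and the 88 students. No score out of 16 is defined in the article, and no pooling of KFPs over cases is described. A reader therefore cannot tell which score the 5%, the 0.8 and the 1.32 refer to, or whether the SD belongs to the same number of items as the difference.

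The layout does not match either. Table 2 counts each student at one level of each factor, whereas in the trial each student contributes two cases at each level of both factors.

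At stake is whether the stated 80% power for a 5% difference applies to the outcome that will be analysed. As written, that is not shown.

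**Working it through.** **1. Inputs.** From Sample size determination: 5% difference, 16 KFPs, SD 1.32, 80% power, two-sided 5% level, total 88. From Outcome measures and Table 1: 8 KFPs per VP and a composite of 8 + 4 + 1 + 2 = 15. From the intervention section: four VPs per student, so two at each level of each factor.

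**2. The plan's own figure.** 0.05 × 16 = 0.8, and 0.8/1.32 = 0.606. For two independent means, 1:1:

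- the normal formula gives 43 per level, total 86;
- the two-sample t-test gives 44 per level, total 88, with power 0.803;
- the main-effect F test of a 2×2 analysis of variance at 88 gives 0.802.

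The figure of 88 is reproduced, so there is no slip in the arithmetic.

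**3. The 5% difference on the scores collected.**

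| Score | 5% of maximum | 0.8 points as a share |
|---|---|---|
| KFPs per VP (8) | 0.40 | 10% |
| Composite per VP (15) | 0.75 | 5.3% |
| Stated basis (16) | 0.80 | 5% |

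**4. A formula that fits the exposure.** For a main effect, take for each student the mean of the two cases with the feature minus the mean of the two without. Let SD be the per-case SD and ρ the correlation between two case scores of the same student, with case effects removed by the model. Each mean of two has variance SD²(1 + ρ)/2, and the two means have covariance ρSD². The variance of the difference is therefore SD²(1 + ρ) − 2ρSD² = SD²(1 − ρ). With n students, the noncentrality is

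δ√n / (SD√(1 − ρ)), tested by a one-sample t-test on n − 1 degrees of freedom.

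**5. KFP score, δ = 0.4, per-case SD assumed to be 1.32.**

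| n | ρ | Noncentrality | Power |
|---|---|---|---|
| 88 | 0 | 0.4 × √88 / 1.32 = 2.843 | 0.803 |
| 112 | 0 | 0.4 × √112 / 1.32 = 3.207 | 0.889 |
| 112 | 0.5 | 3.207 / √0.5 = 4.535 | 0.994 |

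**6. Composite, δ = 0.75, n = 112, ρ = 0.** The article gives no SD for this score, so these values are assumptions.

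| Assumed SD | Noncentrality | Power |
|---|---|---|
| 2.0 | 3.969 | 0.976 |
| 2.5 | 3.175 | 0.883 |
| 3.0 | 2.646 | 0.746 |

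At SD 3.0 and ρ = 0.3 the power is 0.88.

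**7. The independent-groups layout, for comparison.** Keeping 44 v 44 and SD 1.32 with δ = 0.4 gives an effect of 0.303, a total of 344, and power of 0.29 at 88 and 0.36 at 112. With SD 1.32/√2 = 0.93 the total is 174 and power at 88 is 0.51. With SD 0.66 the total is again 88. These figures assume that each student is seen at only one level of a factor, which is not the design.

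**The case against.** The strongest defence is that 16 is not a mistake. Each student meets each factor level in two VPs, and 2 × 8 = 16, so 0.8 over two cases equals 0.4 per case. If 1.32 is the SD of one eight-item case and ρ = 0, the within-student power at 88 is 0.803, the same as the plan's 44 v 44 calculation, and positive correlation only raises it. A reader might infer that no reading makes 0.8, 1.32 and 88 agree. That goes too far, because this one does.

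It remains conjecture. The article does not state it, and Table 1 records the score per VP. On that reading the comparison is within students, so the 44 v 44 layout does not describe it. The agreement also depends on which score the SD belongs to. If 1.32 were the SD of the 16-item sum, within-student power at 88 would be 0.978 at zero correlation, and about 45 students would give 80%.

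Three further points stand in the plan's favour:

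- Using KFPs as a proxy for the composite is disclosed with a reason, and they make up 8 of its 15 items. It is an open choice, not a hidden substitution.
- The item count behind 1.32 may be given in the cited study, which is not at hand. Nothing shows that the SD is wrong; it is only not tied to a score in this trial.
- The 88 does not determine recruitment. The target is 112, from a pool of about 160 + 400 + 150 = 710 students.

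A reader might also infer from step 7 that true power is only 29% to 51%. The documents do not support this, because those figures come from a layout that the trial does not use.

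**Conclusion.** The point holds as an inconsistent planning input of moderate weight. The sample-size section uses 16 KFPs and separate groups of students, while the rest of the article has eight KFPs per VP, a 15-point composite as the analysed outcome, and every student in all four designs. The agreed 5% is 0.4 or 0.75 points on the scores collected, and the article does not connect 0.8 to either.

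It does not show that the trial is underpowered. Within students, 112 gives about 89% (ρ = 0) to 99% (ρ = 0.5) power for 0.4 KFP points, provided the per-case SD is 1.32. For 0.75 composite points at ρ = 0 it falls from about 98% to 75% as the assumed SD goes from 2.0 to 3.0. These results cover main effects only. They assume complete data on all four cases, a common SD and correlation across cases, and case effects handled by the model. The composite SD and ρ are not in the document.

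**What to change.** In Sample size determination and Table 2:

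1. Reconcile the 16 KFPs with the eight per VP. If two cases per factor level are meant, say so.
2. State the 5% difference on the analysed score: 0.75 of 15 per case, or 0.4 of 8 if KFPs remain the proxy. Revise the 0.8 and the 0.6 to match.
3. Give an SD for the same number of items, from the planned pilot if it provides one, or otherwise as a stated range.
4. Restate the power with a within-student formula and a stated range for the correlation, in place of the 44 v 44 layout.

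The cost is a recalculation and some rewording. The standardised effect quoted may become smaller. No change to recruitment, conduct or analysis is shown to be needed.

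### Sample sizes (88/112 for main effects, 352/448 for an equal-sized interaction) are computed for four separate groups of students, although every student completes all four designs; this understates what 112 students can show about the interaction

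*Protocol article*

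**What the plan says.** All references are to the protocol article.

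**Design.** Under Intervention and Independent design variables: "Students will use all four of the case designs during the research". The Abstract says the same and adds that the four randomised groups take the topics in one fixed order, each group meeting the designs in a different sequence.

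**Sample size.** For the KFPs, the SD is taken from an earlier study in which scores were "approximately normally distributed, with a standard deviation of 1.32", and the target is "a difference in mean scores of 0.8, corresponding to a standardised effect size of approximately 0.6". From this, "we would require a total sample size of 88 students to detect this difference with 80% power at the (two-sided) 5% level". For self-reported scores, "a previous study reported a standard deviation of 0.93", the target difference is 0.5, and the total is 112. Table 2 divides these totals among the cells: 22 per cell (44 against 44) and 28 per cell (56 against 56).

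**Interaction.** For an interaction of the same order as the main effects, the article says for KFPs "then we would require a fourfold increase in the sample size to give a total of 352 students", and for self-reported scores "To detect an interaction effect of the same order of magnitude as the expected main effects would require a total of 448 students". It treats 112 as enough for main effects and a large interaction only, with power for other interactions depending on recruitment beyond 112.

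**Analysis.** Data analysis describes one ANCOVA for main effects and their interaction. The blocking factors are randomisation group, case ordering and centre; the covariates are GEM status and gender. The cases are therefore pooled.

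**The concern.** Table 2 places each student in one cell, but the design places each student in all four. With 112 students there are 112 observations per cell, not 28, and both main effects and the interaction are contrasts within students. The sample size section mentions neither repeated observations nor a within-student correlation.

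What is at stake is interpretation rather than the size of the trial. The interaction is part of the primary analysis. A reader who accepts 352 and 448 would take a null interaction at 112 students as badly underpowered, and would also misjudge how small a main effect the trial can detect.

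**Working it through.** **Inputs (Sample size determination):** two-sided 5%, 80% power; KFP 0.8/1.32 = 0.606; self-report 0.5/0.93 = 0.538. The within-student correlation rho is not given, so 0 to 0.5 is assumed. (1.960 + 0.842)² = 7.849.

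**1. The stated figures reproduce as independent groups.** A two-sample t-test needs 44 per level for KFP (total 88) and 56 per level for self-report (total 112). Multiplying by four gives 352 and 448. The arithmetic is right for a parallel 2x2 factorial.

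**2. Within-student variance.** With one observation per cell per student and per-case SD σ:
- main effect: variance σ²(1 − rho)/N, so N = 7.849(1 − rho)/d²
- interaction (difference of differences): variance 4σ²(1 − rho)/N, so N = 4 × 7.849(1 − rho)/d²

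The fourfold ratio between interaction and main effect still holds; only the base changes.

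| | Stated N | rho 0 | rho 0.5 |
|---|---|---|---|
| Self-report, main effect | 112 | 28 | 14 |
| Self-report, equal-sized interaction | 448 | 109 | 55 |
| KFP, main effect (0.8 and 1.32 per case) | 88 | 22 | 11 |
| KFP, equal-sized interaction (same reading) | 352 | 86 | 43 |

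These are normal-approximation values; using the t distribution adds 0 or 1. A simulation of a four-sequence Latin square with student and topic effects agreed for KFP: 24 students gave 82% power for a main effect at rho 0; for the interaction, 88 gave 80% at rho 0 and 44 gave 80% at rho 0.5.

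**3. Self-report interaction of 0.5 at 112 complete students.**
- Parallel layout: SE = 4 × 0.93/√112 = 0.351; ratio 1.42; power about 29%.
- As designed, rho 0: SE = 2 × 0.93/√112 = 0.176; ratio 2.84; power about 81%.
- As designed, rho 0.5 with a student term: SE = 0.176 × √0.5 = 0.124; ratio 4.02; power about 98%.

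**4. Smallest main effect detectable at 112 with 80% power.** 2.802 × √((1 − rho)/112) = 0.26 SD at rho 0 and 0.19 SD at rho 0.5. The plan sizes for 0.54 SD.

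**5. Sensitivity to inputs on which the article disagrees with itself.**
- *16 KFPs against eight per case* (Outcome measures and Table 1). If 16 means two cases summed, with SD 1.32 for the sum, the per-case difference is 0.4 and σ² = 1.32²/(2(1 + rho)). Then N = 42.7(1 − rho)/(1 + rho) for the main effect and four times that for the interaction: about 43 and 171 at rho 0, about 14 and 57 at rho 0.5. Interaction power at 112 and rho 0 is about 62%. If instead the difference is 0.4 per case and 1.32 is the per-case SD, that power is about 36%.
- *5% against 10% for self-report.* The section first names 5% as important for both outcomes, then uses 10% (0.5 of 5). At 5% (0.25), interaction power at 112 and rho 0 is about 29%.
- *Incomplete students.* With the 0.5 difference at rho 0, power is about 78% with 105 completers and 76% with 100.

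**The case against.** **The error is conservative.** This stands. Main effects, which the article calls its primary focus, are not underpowered by it, and nothing about recruitment has to change. Confidence intervals are also planned and will show the precision achieved. The published statement about what 112 students can detect is still wrong for this design.

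**28 per cell is correct for one topic.** Outcome measures describes comparing a case with the same case in another design. Because each group sees one design per topic, that comparison is between different students, and 112 students do give 28 per cell. This defends Table 2 only for a single-topic analysis. The sample size section describes no such analysis, and the planned ANCOVA pools the cases.

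**No student term is listed.** The gain quoted for rho above 0 needs one. The detailed analysis plan may include it, so this is a condition on the figures and not an omission. The rho 0 figures do not depend on it.

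**A tempting stronger reading.** A reader might infer that 112 students have at least 80% power for an equal-sized interaction on both outcomes, so that the 352 and 448 statements can simply be struck out. The article does not support that. It depends on which KFP and self-report differences are meant and on nearly all students completing, while the article plans a complete-case, per-protocol analysis and expects drop-out. Nor is this an arithmetical slip: every stated number reproduces. The fault is the design model to which the arithmetic was applied.

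**Conclusion.** The concern holds in this form: 88/112 and 352/448 are parallel-group figures attached to a design in which each student fills every cell. On the plan's own self-report inputs and any rho of at least 0, the stated totals are about four times too large or more: at most about 28 instead of 112, and about 109 instead of 448. The corresponding interaction power at 112 complete students is at least about 81%, not about 29%. For KFP, the reduction is about fourfold at rho 0 if 0.8 and 1.32 refer to one case (22 and 86), and about twofold if they refer to two cases summed (43 and 171).

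The direction is safe for main effects. What is wrong is the account of the interaction and of the smallest detectable effects. The corrected numbers rest on an assumed rho, on complete students and on the resolution of two internal inconsistencies, so they should be reported as a range rather than as a single guarantee of power.

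**What to change.** Keep the target of 112. Then:

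1. Reconcile the inputs first: 16 KFPs against eight per case, stating what 0.8 and 1.32 refer to; and 5% against 10% for self-reported scores.
2. Recompute the main effects and interaction detectable at 112 from SE(main) = σ√((1 − rho)/N) and SE(interaction) = 2σ√((1 − rho)/N), over a stated range of rho. The planned pilot might inform the range if its students complete more than one case. Allow for incomplete students, and include a student term in the analysis model.
3. Replace the 352 and 448 statements with the recomputed figures; do not merely delete them.
4. Relabel Table 2 so that all N students contribute to each cell, noting that 28 per cell applies only to a comparison within a single topic.

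Cost: one rewritten paragraph and one table. No extra students.
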